### Inclusion and exclusion criteria

#### Inclusion criteria

Psychiatric inpatients between 18–65 years with a primary diagnosis of schizophrenia, bipolar affective disorder, or major depression (ICD-10 Chapter V codes F20 – F29 or F30 – F39). Furthermore, subjects have to be identified as high utilisers of psychiatric inpatient care. In order to avoid misclassification, a two-fold criterion consisting of number of hospitalisations and cumulative LOS prior to the index admission will be applied; a subject will be included for participation if he or she, during a 24-month-period prior to admission: a) has been psychiatrically hospitalised at least twice with a cumulative LOS exceeding 30 days or b) has been psychiatric hospitalised at least once with a cumulative psychiatric LOS of more than 50 days. This criterion is in accordance with existing evidence and is also more comprehensive than the one suggested for psychiatric inpatient care in Germany by Roick et al. [15] who, regardless of LOS, categorised patients as high utilisers who, during a 30-month period, had had more than three admissions.

#### Exclusion criteria

(a) Primary diagnosis of substance abuse; (b) Presence of moderate or severe mental handicap (learning disability) or organic mental disorder; (c) Current treatment by forensic psychiatric services; (d) Insufficient command of the German language in order to receive the intervention, take part in the assessment interviews, and complete patient questionnaires; (e) Lacking capacity to give valid consent to participate; (f) Foreseeable inpatient or day care mental health treatment (including rehabilitation) extending seven days after discharge from psychiatric inpatient treatment.

### Outcome measures

Assessment will take place at baseline and three (3, 6 and 18 months) follow-up measurement points in each participating centre (see Figure 1). Patients will receive a remuneration of 30 € for each assessment. Secondary outcomes will be provided by independent raters (research workers trained in study instrument use), clinicians, and patients. See Table 1 for an overview of the instruments used.

#### Rater perspective (T0 – T3)

Cumulated *LOS *and number of *readmissions *during the study period (primary outcomes) will be assessed by a research worker at T1 – T3 via the German version of the "Client Sociodemographic and Service Receipt Inventory" (CSSRI-EU). This is a standardised instrument for the comprehensive assessment of mental health service use and costs [16] of which a German version is available [17]. It provides detailed information on direct (e.g. hospital in-patient days, out-patient/day care attendances, community-based service contacts, medication profile) and indirect (e.g. days of work loss, state benefits, source/level of income) costs and has been used in a number of German studies^2^.

Assessment of *needs *will be carried out with the German version of the "Camberwell Assessment of Need – European Version" (CAN-EU [18]), an interviewer-administered instrument comprising 22 individual domains of need. Staff and user ratings can be obtained; we administered only the user rating. *Psychopathology *will be assessed using the "Brief Psychiatric Rating Scale" (BPRS [19]) which is a standardised instrument for the assessment of psychopathological symptoms. *Depression *will be tapped into using the "Hamilton Depression Scale" (HAM-D [20]). *Quality of life *will be measured via a) the "Manchester Short Assessment of Quality of Life" (MANSA [21]) which is a disease specific instrument for the multidimensional assessment of objective and subjective quality of life in persons with severe mental illness and b) the EuroQol group's EQ-5D, a generic quality of life assessment instrument which has been developed for the computation of quality adjusted life years (QALYs) and whose psychometric properties and applicability in persons with severe mental illness have been tested [22].

#### Clinician perspective (T0 [inpatient clinician] and T1 [outpatient clinician])

*Psychosocial functioning *will be rated via the "Global Assessment of Functioning Scale" (GAF [23]) which has been shown to be a practical and valid instrument in psychiatric research [24]. Overall *psychological impairment *will be tapped into via the "Clinical Global Impression Scale" (CGI [25]). *Therapeutic relationship *(clinicians' point of view) will be assessed using a retranslated German version of the "Scale to assess the therapeutic relationship in community mental health care" clinician scale (STAR-C [26]).

*Satisfaction with therapeutic work in the ambulatory setting *(T1 only) will be covered with a self-developed scale (ZUF-THERA [27]) consisting of six rephrased items of the ZUF-8 [28], the German version of the "Client Satisfaction Questionnaire" (CSQ [29]). The items were rephrased in that way that outpatient clinicians could give an evaluation of the quality of the given treatment. *Satisfaction with discharge planning *(T1 and intervention group only) will be assessed with a self-developed nine item rating scale.

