## Background

Large numbers of psychic patients do not receive aftercare in the community during the period immediately following hospital discharge. The average rate of utilisation of aftercare is about 50%, with a wide range between 22 and 90% depending on the definition of aftercare [1-3]. More specifically, one third to one half of patients with schizophrenia and related disorders miss their first scheduled outpatient appointment after discharge [4]. In addition, for those who receive follow-up, the delay between discharge and receipt of aftercare (operationalised as first outpatient visit) has been found to be substantial [1,5]. Thus, limited continuity of service provision is pervasive, and time lags arising in this process have been found to increase the probability of relapse and to negatively affect patients' quality of life [1].

There have been some research efforts aimed at identifying the causes for this failure to utilise psychiatric services (for an overview see [2]). Results based on patient variables have been mostly negative, while service system variables, e.g. availability of discharge planning, have been found to facilitate access to aftercare. There is some evidence suggesting that patients who receive discharge planning are more likely to utilise outpatient mental health services and are less prone to become socially isolated and require rehospitalisation. Thus, in a sample of N = 104 inpatients with schizophrenia or schizoaffective disorder, Olfson et al. [6] found that those who had received discharge planning showed significantly better aftercare compliance (98.1 vs. 62.7%), fewer rehospitalisations (40% reduction), and better clinical outcome (34.5 vs. 41.0 BPRS-points, ES = .57) at three-month follow-up. Furthermore, in a sample of 229 inpatients with a primary psychiatric diagnosis, Boyer et al. [1] found that patients were significantly more likely to keep their initial outpatient appointment if they were involved in the outpatient programme before discharge (OR = 2.14 – 3.89) or if the discharge plan was discussed between inpatient staff and outpatient clinicians (OR = 3.17).

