#### Secondary

Subjects receiving the intervention will show better compliance with aftercare as well as better clinical outcome and quality of life. Furthermore, the intervention will show cost-effectiveness and cost-utility, and community-based psychiatrists whose patients receive the new discharge protocol will show better compliance with treatment recommendations.

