#### Patient perspective (T0 – T3)

*Psychological impairment *will be measured using the German version [30] of Derogatis' [31] "Symptom-Check-List" (SCL-90-R), a widely used and validated self-report scale. *Therapeutic relationship *(patients' point of view) will be assessed using the "Scale to assess the therapeutic relationship in community mental health care" patient scale (STAR-P [26]). *Satisfaction with outpatient treatment *(T1 only) will be covered for the outpatient setting with the German version (ZUF-8 [28]) of the "Client Satisfaction Questionnaire" (CSQ [29]). *Satisfaction with discharge planning *(T1 and intervention group only) will be assessed with a self-developed eight item rating scale.

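### GAF and CGI at three months are rated only by the outpatient clinician, so their arm comparison is conditioned on being in aftercare, which the intervention is meant to change

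*Protocol article*

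**What the plan says.** The heading of the clinician-perspective subsection under Outcome measures names the raters: "T0 [inpatient clinician] and T1 [outpatient clinician". GAF, CGI and STAR-C fall under it. Table 1 lists clinician ratings at T0 and T1 and none at T2 or T3, so each of these scales has one post-baseline value. No other T1 rater is named.

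Two T1-only scales presuppose outpatient treatment. ZUF-THERA was reworded so that "outpatient clinicians could give an evaluation of the quality of the given treatment". The patient-rated ZUF-8 "will be covered for the outpatient setting with the German version".

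The secondary hypotheses state: "Subjects receiving the intervention will show better compliance with aftercare as well as better clinical outcome and quality of life". On background rates, the article says: "The average rate of utilisation of aftercare is about 50%, with a wide range between 22 and 90% depending on the definition of aftercare". It also cites a study of discharge planning that found "significantly better aftercare compliance (98.1 vs. 62.7"%.

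Under Statistical analysis, secondary endpoints are differences from T0 in the secondary measures. Clinical outcomes are tested with random-effect regression fitted by GLS, which accepts incomplete cases, under intention-to-treat. GAF and CGI are not treated separately.

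**The concern.** Randomisation protects a comparison when the outcome can be observed in everyone randomised, or when it is missing for reasons unrelated to arm and outcome. Here the T1 value of GAF and CGI needs a treating outpatient clinician. Whether a patient has one three months after discharge is decided after randomisation, and the trial expects the intervention to influence it. If the intervention succeeds, the rated patients in the two arms are differently selected.

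Suppose patients in aftercare tend to be doing better. An intervention that brings harder-to-reach patients into care then adds lower scores to its own arm, and a real benefit on GAF or CGI could be masked. If patients in aftercare tend to be more ill, the distortion favours the intervention.

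The planned safeguards do not address this. Intention-to-treat keeps patients in their allocated arm but cannot supply a rating that was never made. GLS on incomplete data borrows strength from other waves, and these scales have no later one. An analysis plan could not fully repair it either, because the rater is fixed when the data are collected. The switch from inpatient to outpatient rater between T0 and T1 is a separate weakness.

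**Working it through.** The plan gives no figure on this point, so the check asks how large a spurious difference selection alone could produce.

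**Inputs from the article**
- 245 per arm and 10% attrition at each measurement point (Sample size): 245 × 0.9 = 220.5 per arm assessed at T1.
- Aftercare compliance of 62.7% without and 98.1% with discharge planning (Background, one cited sample of 104 inpatients).
- Usual aftercare use of about 50% (Background).

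**Assumptions, not in the article**
- Intervention-arm rates of 65% and 75% against 50%.
- A correlation r between the tendency to be in aftercare and the outcome analysed, taken as 0.1, 0.2 and 0.3.
- Normal selection and no true effect on the outcome.

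**Formula.** If a share p of an arm is rated, the mean outcome of those rated is shifted by r·λ(p) SD, where λ(p) = φ(z)/p and z = Φ⁻¹(p). The spurious difference against the intervention is r·[λ(p_control) − λ(p_intervention)].

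**Values of λ**
- λ(0.50) = 0.3989/0.50 = 0.798
- λ(0.65) = 0.3704/0.65 = 0.570
- λ(0.75) = 0.3178/0.75 = 0.424
- λ(0.627) = 0.3786/0.627 = 0.604
- λ(0.981) = 0.0464/0.981 = 0.047

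**Spurious difference (SD)**

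| Control vs intervention | Difference in λ | r = 0 | r = 0.1 | r = 0.2 | r = 0.3 |
|---|---|---|---|---|---|
| 50% vs 50% | 0 | 0 | 0 | 0 | 0 |
| 50% vs 65% | 0.228 | 0 | 0.02 | 0.05 | 0.07 |
| 50% vs 75% | 0.374 | 0 | 0.04 | 0.07 | 0.11 |
| 62.7% vs 98.1% | 0.557 | 0 | 0.06 | 0.11 | 0.17 |

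A negative r reverses the sign.

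**Effect on a nominal 5% test at r = 0.3**
- 50% vs 65%: 110 vs 143 rated; SE = √(1/110.25 + 1/143.3) = 0.127; 0.068/0.127 = 0.54 standard errors; rejection about 8%.
- 62.7% vs 98.1%: 138 vs 216 rated; SE = √(1/138.3 + 1/216.3) = 0.109; 0.167/0.109 = 1.53 standard errors; rejection about one time in three.

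**Does the baseline score help?** Take r as the correlation with the T1 score and assume a T0–T1 correlation of 0.5. In a simulation at 62.7% vs 98.1%, regression adjustment for T0 reduces 0.06–0.17 SD to 0.04–0.13 SD. It shrinks the bias without removing it. ZUF-8 and ZUF-THERA have no T0 score at all.

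**The case against.** The strongest objection is that r may be close to zero. The Background reports that patient variables have mostly failed to explain non-use of services, while service-system variables do explain access. The Discussion says the same of high utilisers. This is the only evidence in the article that bears on r, and it points to small values. It stands as a limit on size, but it does not show that r is zero.

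Second, a reader might infer that only about half of the controls, the better connected ones, would be rated. The article does not support that. Its 50% concerns the period right after discharge and varies with the definition of aftercare. A patient who misses or delays the first visit may have an outpatient clinician three months later, and no rate for that is given. Likewise, 62.7% vs 98.1% comes from one small sample comparing patients who did and did not receive discharge planning. It is an extreme, not a forecast.

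Third, the 100 € paid to outpatient clinicians in private practice might be taken to make intervention-arm ratings more likely. The fee is for attending the intervention session, not for completing ratings, and Table 1 schedules clinician ratings without restricting them to one arm. That inference should not be drawn.

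Fourth, comparing the bias with the planned 0.2 SD is tempting, but that calculation is framed on inpatient days.

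Fifth, STAR-C, ZUF-THERA and ZUF-8 have no meaning without outpatient care, carry no stated hypothesis, and could not be rescued by another rater. Clinicians' satisfaction with discharge planning ("T1 and intervention group only) will be assessed with a self-developed nine item rating scale") is not an arm comparison. The core of the point is therefore GAF and CGI.

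Finally, the article is condensed, and the full protocol may say what happens when there is no outpatient clinician. The absence of a rating is inferred from the named rater.

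**Conclusion.** The point holds for GAF and CGI at T1. As the plan reads, their only post-baseline value requires an outpatient clinician, the trial expects the intervention to affect aftercare, and the analysis section compares arms on change from T0 without allowing for this. Those comparisons do not have the protection of randomisation.

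Size and sign are unknown. For an assumed r of 0.1–0.3 the spurious difference is 0.02–0.07 SD at 50% vs 65% and 0.06–0.17 SD at the cited extreme. It is zero if r is zero or if selection is the same in both arms.

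A reader might infer that the trial's clinical-outcome claim as a whole is compromised, or that an effective intervention would look harmful. The article supports neither. The primary outcomes, BPRS, HAM-D, SCL-90-R, MANSA and EQ-5D do not depend on an outpatient clinician, nothing makes GAF or CGI the leading clinical measure, and the direction cannot be determined.

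**What to change.** In Statistical analysis:
- rest the comparative clinical-outcome claim on BPRS, HAM-D and SCL-90-R, which are already scheduled at T0–T3 for all patients;
- report, by arm, the share of patients with an outpatient-clinician rating at T1;
- present T1 GAF and CGI as descriptive results among patients in aftercare, and read STAR-C, ZUF-THERA and ZUF-8 in the same way.

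This is a change of wording with no new data collection. Its cost is that GAF and CGI lose comparative status.

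Optionally, if GAF and CGI are to stay comparative, the research worker could rate both at the T0 and T1 interviews, which also keeps the rater the same. This adds a few minutes per interview. Because recruitment began in April 2006, patients already assessed would lack these ratings. The research worker is not blinded, but neither are the clinicians, so nothing is lost on that count.

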#### Patient perspective (T0 – T3)

*Psychological impairment *will be measured using the German version [30] of Derogatis' [31] "Symptom-Check-List" (SCL-90-R), a widely used and validated self-report scale. *Therapeutic relationship *(patients' point of view) will be assessed using the "Scale to assess the therapeutic relationship in community mental health care" patient scale (STAR-P [26]). *Satisfaction with outpatient treatment *(T1 only) will be covered for the outpatient setting with the German version (ZUF-8 [28]) of the "Client Satisfaction Questionnaire" (CSQ [29]). *Satisfaction with discharge planning *(T1 and intervention group only) will be assessed with a self-developed eight item rating scale.

### Sample size

Power calculation for a panel study with four points of assessment was based on the approach suggested by Hedeker et al. [32]. For a high utiliser population, previous research [33] found mean number of inpatient days during 12 months after discharge to be 47 (SD = 83) days (projected mean number for 18 months = 71 days). Based on existing studies, the mean reduction of inpatient days due to the planned intervention was assumed to be 40%. A small effect size (0.2 SD) should be detected with a power of 0.80 at a two-tailed significance level of 0.05. Panel attrition was estimated 10% at each measurement point. With regard to data analysis, a constant group effect over time with a random-effect structure and auto-correlated results was expected. A baseline sample size of 242 participants in each group was calculated to be sufficient.

Accordingly, after rounding to no decimals, a total sample size of 490 participants (N = 98 at each site) will be included in the study. Participants will be randomly assigned to the intervention (N = 245, N = 49 per site) or control group (N = 245, N = 49 per site).

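### The sample size rests on four assessments with a constant group effect, but baseline cannot carry one; if it was counted, power for T1–T3 alone is about 71–74%, not 80%

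*Protocol article*

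**What the plan says.** The Sample size section of the protocol article sets out a "Power calculation for a panel study with four points of assessment". It adds that "a constant group effect over time with a random-effect structure and auto-correlated results was expected". The target is given as: "A small effect size (0.2 SD) should be detected with a power of 0.80 at a two-tailed significance level of 0.05". On loss to follow-up it says: "Panel attrition was estimated 10% at each measurement point". The result is: "A baseline sample size of 242 participants in each group was calculated to be sufficient". The plan rounds this to 245 per group, 490 in total. No value is given for the correlation between assessments.

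Other sections fix where T0 stands:

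- The Overview names the four assessments: baseline, then 3, 6 and 18 months after discharge.
- The section on the pre-discharge session has the intervention worker start from the needs ratings already obtained by the research worker, so T0 comes before the intervention.
- The Rater perspective section says that length of stay (LOS) and readmissions "during the study period (primary outcomes) will be assessed by a research worker at T1 – T3".
- Table 1 lists the service-use inventory (CSSRI-EU) at T0 as well. The Statistical analysis section takes the primary endpoints as differences between T0 and each follow-up, and names a random-effects regression with a constant group effect.

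**The concern.** A constant group effect over four assessments means that each of the four contributes information on the treatment difference. T0 cannot do so. It is measured before the intervention, and randomisation makes the expected group difference there zero. Read as written, the calculation credits the trial with one assessment more than can show an effect, and the number per group comes out too small for the stated power.

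The wording also bears on the analysis. The same constant effect reappears in the Statistical analysis section, where T0 is the reference for the endpoint but its place in the model is not fixed. T0 could be a fourth outcome row, a value to subtract, or a covariate. These three choices give very different precision, and the first also biases the estimate towards zero.

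**Working it through.** **Inputs from the Sample size section.** Effect 0.2 SD; power 0.80; two-sided 0.05; 10% loss at each follow-up, taken as retention 1, 0.9, 0.81, 0.729 at T0–T3; 242 per group calculated, 245 planned. **Assumed, because not given:** the correlation ρ, either exchangeable or AR(1) with equal steps.

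**Formula.** With GLS, free time means and one constant group effect, the variance of the effect is 2/(nJ), where J = Σ p_j s_j. Here p_j is the share of participants with exactly j assessments, and s_j is the sum of all elements of the inverse correlation matrix of size j:

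- exchangeable: s_j = j/(1 + (j−1)ρ)
- AR(1): s_j = (j − (j−2)ρ)/(1 + ρ)

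Then n = 2(1.960 + 0.842)²/(0.2² J) = 15.70/(0.04 J), and power = Φ(0.2√(nJ/2) − 1.960).

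**Step 1: reproduce 242 with four assessments.** Shares 0.10, 0.09, 0.081, 0.729.

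- Exchangeable, ρ = 0.434: J = 0.10 + 0.09×1.395 + 0.081×1.606 + 0.729×1.738 = 1.622, so n = 242.
- AR(1), ρ = 0.594: J = 0.10 + 0.09×1.255 + 0.081×1.509 + 0.729×1.764 = 1.621, so n = 242.

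**Step 2: drop T0 at the same ρ.** Shares 0.09, 0.081, 0.729 for one, two and three follow-ups.

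- Exchangeable: J = 0.09 + 0.081×1.395 + 0.729×1.606 = 1.374. With n = 245, power = Φ(2.594 − 1.960) = 73.7%; 80% needs 286 per group.
- AR(1): J = 0.09 + 0.081×1.255 + 0.729×1.509 = 1.292. Power = Φ(2.516 − 1.960) = 71.1%; 80% needs 304 per group.

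Re-solving ρ under other attrition patterns, under the actual 0/3/6/18-month spacing, or with an equal-weight contrast in place of GLS gives about 70–77% at 242 per group, and about half a point more at 245.

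**Step 3: does 242 prove that T0 was counted?** No. With only three effect-carrying assessments, 242 is met at ρ = 0.28 (exchangeable) or 0.36 (AR(1)). For example, 0.09 + 0.081×2/1.278 + 0.729×3/1.556 = 1.622.

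**Step 4: the three roles of T0, with 245 per group and the ρ of step 1.**

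| Role of T0 | Exchangeable | AR(1) |
|---|---|---|
| Subtracted (unadjusted change) | 66% | 67% |
| Fourth outcome row under the constant effect | estimate 0.136 SD, power 48% | estimate 0.118 SD, power 38% |
| Covariate | 87% | 84% |

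- *Change, exchangeable.* Differences have variance 2(1−ρ) = 1.132 and mutual correlation 0.5, so J = (0.09 + 0.081×2/1.5 + 0.729×3/2)/1.132 = 1.141 and power is Φ(2.364 − 1.960) = 66%.
- *Outcome row, exchangeable.* The T0 row contributes zero, so the estimate is 0.2 × (0.09/1.434 + 0.081×2/1.868 + 0.729×3/2.302)/1.622 = 0.2 × 1.100/1.622 = 0.136 SD.
- *Covariate, exchangeable.* If T0 correlates b with every follow-up, s_j becomes s_j/(1 − b²s_j). With b = 0.434, J = 0.09×1.232 + 0.081×1.892 + 0.729×2.303 = 1.943 and power is Φ(3.085 − 1.960) = 87%.
- *Covariate, AR(1).* Each s_j gains ρ²/(1−ρ²) = 0.545, so J = 1.292 + 0.9×0.545 = 1.783 and power is 84%.

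**Step 5: a weaker baseline correlation.** With the follow-ups exchangeable at 0.434 and b = 0.1 or 0.3, J = 1.395 or 1.597, so power is 74% or 80%. With the follow-ups AR(1) at 0.594, J = 1.311 or 1.487, so power is 72% or 77%.

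**The case against.** The strongest reply is that four assessments may simply describe the panel, as the Overview does, and that the underlying calculation may have used three effect-carrying assessments. Step 3 shows that the number per group cannot settle this, and the correlations it would need are no less plausible than those in step 1. This stands, and it makes the shortfall conditional. It does not rescue the paragraph: if three were used, the sentence naming four beside a constant effect needs correcting.

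A second reply is that T0 service use is collected and enters the endpoint, so an analysis ignoring T0 is not the plan. This also stands. It would be wrong to infer that nothing on the primary measure exists at T0: Table 1 and the Statistical analysis section show otherwise. Yet the endpoint as worded, a difference from T0, still has only three contrasts that can show an effect, and without adjustment it yields less power than T1–T3 alone.

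Third, the article's own effect assumption exceeds 0.2 SD. It cites a "mean number of inpatient days during 12 months after discharge to be 47 (SD = 83) days" and says that "the mean reduction of inpatient days due to the planned intervention was assumed to be 40" per cent. That is 0.40×47 = 18.8 days, or 18.8/83 = 0.227 SD, for which T1–T3 alone gives 84% or 81% with 245 per group. This is true, but the stated target is 0.2 SD, and the stated power belongs to that.

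Finally, the article condenses a fuller protocol that is not shown, so the missing correlation is not in itself a fault. The point rests on what the article does state.

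**Conclusion.** The point holds in conditional form. The paragraph pairs four assessments with a constant group effect although only three can carry one. If T0 was counted, at the correlation that reproduces 242, the power for T1–T3 alone at 0.2 SD is about 71–74%, and about 70–77% across variants.

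A reader might go further and conclude that the trial is underpowered at 71–74%. The document does not support that: the correlation is back-solved, not stated, and 242 is equally consistent with three assessments. A reader might also infer that the planned model will shrink the effect to 0.12–0.14 SD with 38–48% power. That would require raw T0 values as outcome rows, which the Statistical analysis section does not state; its wording points to differences from T0, at about 66–67%. The dilution is a risk left open by the wording, not the stated plan.

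All figures assume equal variances across assessments and the attrition pattern given above. The figures for the role of T0 also depend on how strongly T0 service use correlates with follow-up.

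**What to change.** In the Sample size section, restate the power for three post-baseline assessments and give the assumed correlation and its structure. In the Statistical analysis section, define the primary model on T1–T3 with a constant group effect and with T0 service use as a covariate, neither as a fourth outcome row nor as a subtracted change score.

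Report the resulting power as a range for the same 490 participants: about 84–87% at the implied correlations, and about 74–80% if T0 correlates only 0.1–0.3 with exchangeable follow-ups (72–77% if they are AR(1)). The lower part deserves showing, because patients are selected on prior inpatient use, which may weaken the baseline correlation.

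The cost is wording in two paragraphs. No further patients or assessments are needed, since the T0 inventory is already planned. The downside is that the stated power may become slightly less favourable than 80%.

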### Overview

NODPAM is a randomised controlled prospective trial with four measurement points during an 18-month study period (see Figure 1, upper part). Assessments will take place at baseline, three, six, and 18 months after discharge. We believe that this design is appropriate to answer the research questions since on one hand it allows to examine the short-term (three months after baseline), mid-term (six months) and long-term (18 months) effects of the intervention, and on the other hand, the burden on participants (patients and clinicians) is not too high which will help to keep low study attrition. In the event of rehospitalisation, data assessment will proceed as originally scheduled, allowing some delay in case the patient should be in an acute crisis making assessment impossible. Assessment will be carried out by a research worker (different in person from the intervention worker).

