### Statistical analysis

The primary endpoints will be derived from the difference in LOS and number of hospitalisations between T0 and T1, T2, and T3. The secondary endpoints will be calculated from the differences in sum (or – if applicable – subscale) scores of the secondary outcome measures between T0 and T1, T2, and T3. Multiple measurement points have been chosen in order to scrutinise the intervention's effect over time, especially the question of whether short- and mid-term effects would persist.

Analyses will start once baseline data have been collected and cleaned. Descriptives of all outcome measures will be produced, and outcome trajectories from T0 – T3 will be examined via exploratory analyses. The effect of the intervention on reduction of number of inpatient days as well as on clinical outcomes, quality of life, and compliance will be tested by means of random-effect regression models including a constant group effect across time [35-37]. Due to the application of a generalised least square (GLS) estimation weighted for the lengths of the time series for each case, these models allow the inclusion of cases with incomplete (unbalanced) data across panels. Due to expected skewness of the primary dependent variable (LOS), bootstrapping methods will be applied for the estimation of standard errors and confidence intervals. Cost-effectiveness of intervention will be tested by means of the net-benefit approach [38], and its cost-utility by using QALYs generated from EQ-5D.

Analysis will be carried out according to the principle of intention-to-treat. In case attrition should exceed the projected rate of 10%, additional per-protocol analysis will be performed.

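### The sample size credits a constant 0.2 SD at four assessments, but the only SD given is for a 12-month total; with an evenly spread effect, power for 0.2 SD at 242 per group is below the stated 0.80

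*Protocol article*

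**What the plan says.** All references are to the Protocol article.

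- **Sample size, outcome inputs.** Earlier research in high utilisers found a "mean number of inpatient days during 12 months after discharge to be 47 (SD = 83) days (projected mean number for 18 months = 71 days". No 3-month or 18-month SD is given.
- **Sample size, effect.** "the mean reduction of inpatient days due to the planned intervention was assumed to be 40" per cent. "A small effect size (0.2 SD) should be detected"; the target is that it "should be detected with a power of 0.80 at a two-tailed significance level of 0.05".
- **Sample size, model.** The calculation is described as a "Power calculation for a panel study with four points of assessment", and "a constant group effect over time with a random-effect structure and auto-correlated results was expected". Attrition is put at 10% at each measurement point. The result is 242 per group, rounded up to 245 per group and 490 in total. No correlation is printed.
- **Overview.** "Assessments will take place at baseline, three, six, and 18 months after discharge".
- **Outcome measures, rater perspective.** LOS and readmissions during the study period are collected at T1 to T3. The period that LOS covers at each visit is not stated.
- **Statistical analysis.** "The primary endpoints will be derived from the difference in LOS and number of hospitalisations between T0 and T1, T2, and T3". The model is a random-effect regression with a constant group effect across time.

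**The concern.** A repeated-measures calculation with a constant standardised effect suits an outcome read afresh at each visit, such as a symptom score. Inpatient days are different: they accumulate over a window, and both their mean and their SD depend on its length. The only SD in the plan belongs to a 12-month window, while the gaps between assessments are 3, 3 and 12 months.

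Two conditions then pull against each other. A 3-month window has the same standardised effect as the 12-month total only if a patient's quarters are perfectly correlated. Several waves improve precision only if they are not. In addition, one of the four waves is baseline, before any effect can appear.

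At stake is how a null result is read. Readers would take 0.80 power for 0.2 SD at face value and treat a non-significant result as fairly strong evidence against a reduction of about 35% in inpatient days.

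**Working it through.** **1. Inputs.** From Sample size: mean 47, SD 83 (12 months), reduction 40%, effect 0.2 SD, two-sided 0.05, power 0.80, four assessments, 10% attrition per point, 242 per group. From Overview: visits at 0, 3, 6 and 18 months. My assumptions: LOS per interval (0-3, 3-6, 6-18 months); quarters with equal means and SDs; exchangeable or AR(1) correlation r; effect proportional to window length.

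**2. Reproducing 242.** For a difference averaged over T visits, n = 2(1.96 + 0.84)² × v / d², where v is the variance of the averaged visit means in SD² units. With d = 0.2, 2 × 2.8016² / 0.04 = 392.4, so one comparison needs 393 per group. With four visits, retention 1, 0.9, 0.81, 0.729 and exchangeable r = 0.40:

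- variances: 1 + 1.111 + 1.235 + 1.372 = 4.717
- covariances: 2 × 0.40 × (3 × 1 + 2 × 1.111 + 1.235) = 5.165
- v = (4.717 + 5.165) / 16 = 0.618
- n = 392.4 × 0.618 = 242.4

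GLS with AR(1) r = 0.6 gives 243.8. The printed figure is therefore recovered when a full 0.2 SD is credited at all four assessments.

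**3. Scale of the effect.** 0.40 × 47 = 18.8 days, and 18.8/83 = 0.227 SD. Conversely 0.2 × 83 = 16.6 days, and 16.6/47 = 35%. Spread evenly, a quarter carries 16.6/4 = 4.15 days.

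**4. Effect in a 3-month window.** Quarterly SD = 83 / √(sum of the 4 × 4 correlation matrix).

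| Correlation | Matrix sum | Quarterly SD | 4.15 / SD |
|---|---|---|---|
| 0 | 4 | 41.5 | 0.100 |
| Exchangeable 0.4 | 8.8 | 28.0 | 0.148 |
| AR(1) 0.5 | 8.25 | 28.9 | 0.144 |
| AR(1) 0.6 | 9.472 | 27.0 | 0.154 |
| 1 | 16 | 20.75 | 0.200 |

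Only the last row gives 0.2 SD. There the waves duplicate each other, and power at 242 per group without dropout is Φ(0.2 × √(242/2) − 1.96) = Φ(0.24) ≈ 0.595.

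**5. Power with T1-T3 only.** λ = √[(n/2) δ′Iδ], where δ holds the effects in days for the three windows. I is the sum, over dropout patterns, of the pattern's share times the inverse covariance of the windows observed. Power = Φ(λ − 1.96), n = 242, retention 0.9, 0.81, 0.729.

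| Correlation | 0.2 SD, attrition | 0.2 SD, no dropout | 40%, attrition | 40%, no dropout |
|---|---|---|---|---|
| Exchangeable 0.4 | 0.557 | 0.636 | 0.664 | 0.743 |
| AR(1) 0.5 | 0.629 | 0.722 | 0.736 | 0.823 |
| AR(1) 0.6 | 0.618 | 0.706 | 0.726 | 0.809 |
| All r, both structures | 0.55-0.66 | 0.60-0.77 | 0.66-0.76 | 0.70-0.86 |

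**6. Splitting the loss.** Dropping T0 but keeping a flat 0.2 SD in the three windows, with the same correlations and attrition, gives 0.713, 0.779 and 0.739. The further fall from the SD mismatch is 0.713 − 0.557 = 0.156, 0.779 − 0.629 = 0.150 and 0.739 − 0.618 = 0.121, or about 12-16 points.

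**7. Detectable reduction at 80% power, with attrition.** This is 16.6 × 2.80/λ, with λ = 2.10, 2.29 and 2.26. It gives about 22.1, 20.3 and 20.6 days per 12 months, or 43-47% of 47.

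**8. SD at 18 months.** 83 × √1.5 = 101.7 days if quarters are independent; 83 × 1.5 = 124.5 if perfectly correlated. An effect of 16.6 × 1.5 = 24.9 days is then 0.245 or 0.20 SD. A two-group test on the total without dropout has power 0.77 or 0.60, the same range as in step 5.

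**The case against.** Much of the check rests on things the article does not say.

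- **Windows and derivation of 0.2.** The recall window is not given, and the text never says that 0.2 comes from 18.8/83 or that SD 83 was applied at each wave. This stands; these are inferences. But no other SD is offered. With complete data, LOS cumulated to each visit is a linear re-expression of the same windows, so that reading does not restore 0.80 for 0.2 SD.
- **Effect pattern.** The intervention targets the transition out of hospital, with sessions just before discharge and at three months, so an early effect is plausible. As an illustration, weight the six quarters 1.5, 1.2, 0.7, 0.6, 0.6, 0.6, which keeps the 12-month total. With compounding attrition, power rises to 0.69-0.72 for 0.2 SD and 0.80-0.82 for 40%. This stands, and it limits the conclusion to an even effect.
- **Attrition and target.** The Statistical analysis section speaks of a projected rate of 10%, which could mean a single loss. With a flat 10% loss, AR(1) 0.5-0.6 and a 40% reduction, power is 0.77-0.78, and without dropout 0.81-0.82. So the full 40% reduction can come close to 0.80 or pass it.
- **Analysis model.** The planned model is not the optimal GLS used here, and adjustment for pre-admission LOS could raise power. That is fair, but such adjustment is not part of the stated calculation.
- **A condensed article.** An unprinted correlation is no fault in an article. The point is that the inputs and the result that are printed do not fit together.

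A reader might also infer that the true power is 56-63%. The documents do not support a fixed figure: it needs a correlation solved backwards from 242 with baseline counted as a wave.

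**Conclusion.** The point holds in conditional form. The 242 per group is recovered by crediting 0.2 SD at four assessments, one of them baseline, while the only SD describes a 12-month total. With LOS per interval and an even effect, power for 0.2 SD stays below 0.80 at every correlation, with or without dropout. For the 40% reduction it also stays below 0.80 if attrition compounds as the Sample size section suggests, but not necessarily with little dropout or a front-loaded effect.

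Two stronger readings should be resisted. The SD mismatch does not explain the whole shortfall: counting T0 accounts for part of it, since three flat waves already give only 0.71-0.78. Nor are the 3-month effects drastically smaller at the correlations near those that reproduce 242: they are 0.14-0.15 SD, and fall to 0.10 SD only with independent quarters.

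**What to change.** Keep N = 490 and redo the sample-size paragraph.

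1. Base it on total inpatient days over the 18-month follow-up, or on the T1-T3 windows with an SD for each window. Do not count T0 as an outcome wave.
2. Project the SD to 18 months along with the mean: about 102 days if quarters are independent, up to 124.5 if perfectly correlated.
3. State the LOS window at each visit, the assumed correlation, the effect pattern over time and how attrition accumulates.
4. Replace 0.80 with the power range that follows, or with the reduction detectable at 80% power. With an even effect and correlations near those that reproduce 242, that reduction is about 43-47%. Do not print 0.56-0.63 as a fixed figure, because it depends on a correlation the document does not give.

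The cost is a revised paragraph and probably a less favourable power statement. No patients, visits or instruments are added.
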